## 9.3 Reporting of Serious Adverse Events

All events meeting the definition of a serious adverse event should be reported according to the departmental SAE checklist and SAE form. The initial SAE form should be sent to the following within 24 hours / 1 business day of the Principal Investigator becoming aware:

1. Investigator-Sponsor
2. crssafety [contact]
3. Local Institutional Review Board when reporting requirements are met.

4. Horizon –  
Email: [[contact]](mailto:[contact])  
[contact]

In addition to completing appropriate patient demographic and suspect medication information, the report should include as applicable the following information that is available at the time of report within the Sections B and C of the departmental SAE form:

- CTCAE v5.0 term(s) and grade(s)
- current status of study drug
- all interventions to address the AE (testing and result, treatment and response)
- hospitalization and/or discharge dates
- event relationship to study drug

Follow-up reports:

Additional information may be added to a previously submitted report by adding to the original departmental SAE form and submitting it as follow-up or creating supplemental summary information and submitting it as follow-up with the original departmental SAE form.

#### **9.4 Reporting adverse events to the responsible IRB**

In accordance with applicable policies of the University of Pittsburgh Institutional Review Board (IRB), the PI will report to the IRB any observed or volunteered adverse event that is determined to be 1) associated with the investigational drug or study treatment(s); 2) a serious adverse event (SAE, described in section 9.1); or 3) an unexpected, suspected adverse reaction (defined in section 9.1). Adverse event reports will be submitted to the IRB in accordance with the respective IRB procedures.

Applicable adverse events will be reported to the IRB as soon as possible and, in no event, later than 10 calendar days following the investigator's receipt of the respective information. Adverse events which are 1) associated with the investigational drug or study treatment(s); 2) fatal or life-threatening; and 3) unexpected will be reported to the IRB within 24 hours of the investigator's receipt of the respective information.

Follow-up information to a reported adverse event will be submitted to the IRB as soon as the relevant information is available. If the results of the investigator's follow-up investigation show that an adverse event that was initially determined to not require reporting to the IRB does, in fact, meet the requirements for reporting, the investigator will report the adverse event to the IRB as soon as possible, but in no event later than 10 calendar days, after the determination was made.

Expected AEs listed in section 9.2 will not be reported but will be described in a case report form and summarized in the annual report of the protocol.

Adverse events related to the subject's pre-existing or undiagnosed conditions or concurrent therapies or medication will not be collected or reported.

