### 6.9 Management of Other Complications

- 6.9.1 Cytopenia, GVHD, and infection: Management of cytopenia, GVHD, and infection will be per the institutional Standard Practice Guidelines. These complications could be due in part or in full to IFN- $\gamma$ , DLI, or the side effects of the transplant itself.

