## **8. STATISTICAL CONSIDERATIONS**

### **8.1 Study Endpoint**

#### **8.1.1 Primary safety endpoint:**

To evaluate the adverse events of IFN-γ in relapsed patients after alloSCT, per CTCAE v5.0

To evaluate the adverse events of IFN-γ in relapsed patients after alloSCT with concurrent use of donor lymphocyte infusion, per CTCAE v5.0

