##### **8.1.1.1 Analysis plan**

Adverse events will be summarized via descriptive statistics. The maximum grade of toxicity for each category of interest will be recorded for each patient and the summary results will be tabulated by category and grade.

The following data will be reported

- Incidence of graft-versus-host disease (GVHD) progression
- Incidence of de novo GVHD
- Incidence of serious adverse events (SAE) or grade 3 or 4 unexpected, suspected adverse reaction defined in section 9.1

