Unexpected, suspected adverse reaction: A suspected adverse reaction is considered “unexpected” if it is not listed in the general investigational plan or clinical protocol, or is not listed at the specificity or severity that has been previously observed and/or specified. If an investigator brochure is not required or available, suspected adverse reaction is not consistent with the risk information described in the general investigational plan or elsewhere in the current application, as amended. “Unexpected,” as used in this definition, also refers to adverse events or suspected adverse reactions that are mentioned in the investigator brochure as occurring with a class of drugs or as anticipated from the pharmacological properties of the drug, but are not specifically mentioned as occurring with the particular drug under investigation. Any clinically important increase in the rate of a serious suspected adverse reaction over that listed in the protocol or investigator brochure can also be considered unexpected. An aggregate analysis of specific events observed in a clinical trial (such as known consequences of the underlying disease or condition under investigation or other events that commonly occur in the study population independent of drug therapy) that indicates those events occur more frequently in the drug treatment group than in a concurrent or historical control group.

All observed or volunteered adverse events (serious or non-serious), regardless of a study group or suspected causal relationship to the study drug(s) will be recorded in the subjects’ case histories. For all adverse events, sufficient information will be pursued and/or obtained so as to permit 1) an adequate determination of the outcome of the event (i.e., whether the event should be classified as a serious adverse event) and 2) an assessment of the causal relationship between the adverse event and the study drug(s). All toxicities encountered during the study will be evaluated on an ongoing basis, according to the NCI Common Toxicity Criteria version 5.0.

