## **13. DATA SAFETY MONITORING PLAN**

Investigator/Sub-investigators, regulatory, CRS management, clinical research coordinators, clinical research associates, data managers, and clinic staff meet regularly in disease center Data Safety Monitoring Boards (DSMB) to review and discuss study data to include, but not limited to, the following:

- serious adverse events
- subject safety issues
- recruitment issues
- accrual
- protocol deviations
- unanticipated problems
- breaches of confidentiality

Minutes from the disease center DSMB meetings are available to those who are unable to attend in person.

All toxicities encountered during the study will be evaluated on an ongoing basis according to the NCI Common Toxicity Criteria Version 5.0. All study treatment associated adverse events

that are serious, at least possibly related and unexpected will be reported to the IRB. Any modifications necessary to ensure subject safety and decisions to continue or close the trial to accrual are also discussed during these meetings. If any literature becomes available which changes the risk/benefit ratio or suggests that conducting the trial is no longer ethical, the IRB will be notified in the form of an Unanticipated Problem submission and the study may be terminated.

All study data reviewed and discussed during these meetings will be kept confidential. Any breach in subject confidentiality will be reported to the IRB in the form of an Unanticipated Problem submission. The summaries of these meetings are forwarded to the UPMC Hillman Cancer Center DSMC which also meets monthly following a designated format.

For all research protocols, there will be a commitment to comply with the IRB's policies for reporting unanticipated problems involving risk to subjects or others (including adverse events). DSMC progress reports, to include a summary of all serious adverse events and modifications, and approval will be submitted to the IRB at the time of renewal.

Protocols with subjects in long-term (survival) follow-up or protocols in data analysis only, will be reviewed bi-annually.

Both the UPMC Hillman Cancer Center DSMC as well as the individual disease center DSMB have the authority to suspend accrual or further investigate treatment on any trial based on information discussed at these meetings.

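### The last sentence of Protocol 9.4 bars collection of adverse events attributed to other causes, contradicting 9.1 and letting attribution filter the primary safety data

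*Protocol*

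**What the plan says.** Four parts of the Protocol bear on which adverse events are captured.

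- **9.4, last sentence:** events related to the subject's "pre-existing or undiagnosed conditions or concurrent therapies or medication will not be collected or reported".
- **9.4, the sentence before it:** "Expected AEs listed in section 9.2 will not be reported but will be described in a case report form", with an annual summary. The list in 9.2.3 covers acute GVHD (up to 61%), chronic GVHD, marrow aplasia and infusion reaction after DLI. The list in 9.2.4 covers cytopenias, treatable infections and other transplant complications.
- **9.1:** all adverse events, serious or not, "regardless of a study group or suspected causal relationship to the study drug(s) will be recorded" in the case histories.
- **8.1.1 and 8.1.1.1:** the second primary safety endpoint is "To evaluate the adverse events of IFN-γ in relapsed patients after alloSCT with concurrent use of donor lymphocyte infusion, per CTCAE v5.0". The reported outputs include "Incidence of graft-versus-host disease (GVHD) progression" and de novo GVHD, with no condition on attribution.

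On attribution, 6.9.1 says that cytopenia, GVHD and infection "could be due in part or in full to" IFN-γ, DLI or the transplant itself.

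On IRB reporting, 9.4 begins by requiring a report of any serious adverse event and then exempts the events listed in 9.2. Section 13 says that treatment-associated events "that are serious, at least possibly related and unexpected will be reported to the IRB".

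**The concern.** The primary safety endpoint is a descriptive count of adverse events in a small, uncontrolled pilot. Its value depends on capturing every event first and judging cause second. The last sentence of 9.4 reverses that order: an event attributed to baseline disease or to another therapy is not collected at all.

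That attribution is hard to make in these patients. They have relapsed after transplant, may enter with stable GVHD, and may have had a hypomethylating agent, venetoclax or targeted therapy within the prior four weeks (3.2.11 exempts these from the chemotherapy washout). Most go on to DLI if the plan succeeds. An investigator following 9.4 in good faith could leave out an event that IFN-γ caused or contributed to. The error has one direction, since the rule can only take events away. Two institutions could also apply it differently.

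**Working it through.** The plan has no sample-size, power or alpha figure that bears on this, so the check is a comparison of text, with one small calculation to show scale.

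**Step 1. Does the sentence concern collection, or only IRB reporting?** It sits in an IRB-reporting section, but it names collection as well as reporting. The preceding sentence of 9.4 separates the two acts: listed events are not reported, yet they do go on a case report form. Section 9.5 also uses collection to mean capture of adverse events. The literal reading is therefore a bar on capture.

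**Step 2. Does 9.1 settle it?** It contradicts the sentence but does not override it. 9.1 secures an entry in the case history. The data shared between sites are those in the electronic case report form (10.1). A site could satisfy 9.1 in its source record and still leave the event off the form under 9.4.

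**Step 3. Which events are affected?**

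| Event type | Order to capture | Order not to collect | Result |
|---|---|---|---|
| GVHD progression or de novo GVHD | 8.1.1.1 outputs, Stage 2 visit assessments, 9.2.3 with the CRF sentence of 9.4 | 9.4 last sentence, if attributed to DLI or to GVHD present at entry | Conflicting orders |
| Other events listed in 9.2.3 or 9.2.4 | CRF sentence of 9.4, 9.1 | 9.4 last sentence, if attributed elsewhere | Conflicting orders |
| Serious events | 9.3, 9.1 | 9.4 last sentence, if attributed elsewhere | Conflicting orders |
| Non-serious, non-GVHD, outside the 9.2 lists, attributed to DLI, other therapy or baseline disease | 9.1 (case history); DLI reactions are also assessed at Stage 2 visits | 9.4 last sentence | Most exposed: no explicit CRF route |

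The edge of the last row cannot be drawn exactly, because 9.2.2 takes its list from the prescribing information, which the Protocol does not reproduce.

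**Step 4. Scale.** Inputs: 8.2.1 aims for at least three patients with DLI in each cohort and anticipates about six enrolled. 9.2.3 gives acute GVHD after DLI as up to 61%, which is an upper figure. The rates of 20% and 40% are my assumptions, used to show a range. Expected cases are n × p, and the chance of at least one is 1 − (1 − p)^n.

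| n with DLI | p | Expected cases | P(at least one) |
|---|---|---|---|
| 3 | 0.20 | 0.60 | 0.488 |
| 3 | 0.40 | 1.20 | 0.784 |
| 3 | 0.61 | 1.83 | 0.941 |
| 6 | 0.20 | 1.20 | 0.738 |
| 6 | 0.40 | 2.40 | 0.953 |
| 6 | 0.61 | 3.66 | 0.997 |

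These are chances that the conflicting orders will meet a real GVHD case, not counts of events lost. For any event type, one patient's missed event changes a reported incidence by 1/6 = 17 percentage points with six patients and by 1/3 = 33 points with three.

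**Step 5. IRB rules within 9.4.** Its opening requires any serious event to be reported. Its exemption for 9.2 events has no severity limit: 9.2.1 is restricted to grades 1 to 2, but 9.2.3 and 9.2.4 are not. A serious acute GVHD case after DLI is thus both reportable and exempt. Section 9.3 does not resolve this, because it sends the form to the local IRB only if that board's reporting requirements are met.

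**The case against.** The strongest defence is that this is one loose sentence in an IRB-reporting section, outweighed by everything around it. GVHD progression and de novo GVHD are named outputs. The Stage 2 and follow-up visits assess reactions to IFN-γ or DLI with a focus on GVHD. Events listed in 9.2 go on the case report form. Serious events go to the sponsor under 9.3. DLI may not be a concurrent therapy in the sense of 9.4 at all: it is a protocol stage, it is listed under treatment in both schedules of events, and 9.4 itself speaks of study treatments in the plural.

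Much of this stands, and it rules out three stronger readings.

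- *That 9.4 removes DLI-related and GVHD events from the primary endpoint.* It does not. Those events have separate capture routes, and the Protocol never says whether DLI is a concurrent therapy or a study treatment. 8.1.1 does call its use concurrent, so the term remains ambiguous.
- *That the GVHD count could fall from about four in six to none.* This would require ignoring the CRF sentence, 8.1.1.1 and the visit schedule together, and treating an upper bound of 61% as the expected rate.
- *That Section 13 flatly contradicts 9.4, or that a fatal expected GVHD case would bypass the IRB.* Section 13 does not say that only those events are reported, and it sends the IRB a summary of all serious events at renewal. The suspension rule in 8.4.1 turns on attribution of a death to IFN-γ and does not pass through the expected-event exemption.

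What the defence does not answer is that the sentence says collected, that it contradicts 9.1, and that the events in the last row of the table have no explicit route to the form.

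**Conclusion.** The point holds as an internal contradiction that is wrong as written. Section 9.4 permits omission of events from the primary safety data on a causality judgement that 6.9.1 concedes may not be possible, and the resulting error can only lower the count. GVHD and 9.2-listed events face conflicting orders. Non-serious, non-GVHD events outside those lists are the ones realistically at risk.

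The number of events lost cannot be estimated from the Protocol; it depends on how each site reads the sentence and how often it attributes events elsewhere. The size argument rests only on the small denominators. The conclusion assumes that sites apply the sentence literally. If every site reads it as an IRB-reporting rule, no data are lost, but nothing in the text secures that reading. The conflict within 9.4 over serious events that are also listed in 9.2 is a second, smaller point that needs one clarifying statement.

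**What to change.** 1. Delete the last sentence of 9.4, or confine it to expedited IRB reporting with no mention of collection.
2. State in 9.1 or 9.5 that every adverse event from signed consent, the start that 9.5 already sets, is entered on the case report form regardless of attribution. Record the attribution (IFN-γ, DLI, underlying disease, other therapy) alongside it.
3. State in 8.1.1.1 that the primary safety table counts all such events. Attribution can be displayed but is not a condition for entry.
4. In 9.4, say whether the exemption for 9.2 events covers serious adverse events, and align the wording of Section 13 with the answer.

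The cost is a short text amendment, a few more form lines per patient and a reported event rate that will look less favourable. If the sentence was already in force for patients treated so far, the case histories required by 9.1 can be checked against the forms for omitted events.

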#### **9.5 Time Period for Collecting Adverse Events**

Collection of adverse events will begin after the subject sign the informed consent form and will end at either time point described below, whichever occurs later

For subjects who completed the IFN- $\gamma$  therapy: At the protocol visit #8: 28 days (+/- 5 days) safety assessment after the last dose of IFN- $\gamma$  therapy (Off treatment assessment) defined on section 6.5.9

For subject who meet the criteria for removal from the study: At off study visit as defined on section 8.3.2.

## **10. DATA MANAGEMENT PLAN**

### **10.1 Clinical Data Management**

All human subjects personally identifiable information (PII) as defined in accordance with the Health Insurance Portability and Accountability Act, eligibility, and consent verification will be recorded in CTMA. Primary data obtained during the conduct of the protocol will be kept in secure network drives or in approved alternative sites that comply with UPMC/ University of Pittsburgh security standards. At Fred Hutchinson Cancer Research Center, primary data will be kept in their secure network drives that comply with the security standards of Fred Hutchinson Cancer Research Center. Deidentified data in electronic case report form (eCRF) will be then shared using a secure web-based SharePoint that complies with UPMC/University of Pittsburgh security standards.

### **10.2 Genomic Data Management**

The coded sequenced data will be stored in a password-protected secure database that complies with UPMC/ University of Pittsburgh security standards.

### **10.3 End of Study Procedures**

Data will be stored in locked cabinets or in a password protected database until it is no longer of scientific value.

### **10.4 Loss or Destruction of Data**

Should we become aware that a major breach in our plan to protect patient confidentiality and trial data has occurred, the IRB will be notified.

Any breaches of confidentiality will be brought to the attention of the principal investigator and co-investigators for analysis and action. Data reviewed and discussed during these meetings will be kept confidential. Any breaches in subject confidentiality will be reported to the IRB.

### **10.5 Incidental/Secondary Findings Disclosure Procedure**

Nucleotide sequence variations to be determined in these studies are not known to be associated with any known disease, and the research laboratory test used to identify the sequencing is not the Clinical Laboratory Improvement Amendments (CLIA)-certified for clinical testing. For all these reasons, the genetic information obtained cannot be meaningfully

interpreted outside the narrow focus of the study and will not be provided to the subjects or their physicians.

## **11. RISK AND BENEFIT**

As described in the introduction, post-transplant relapse harbors very high risk of mortality even with current best standard of care (greater than 80-90% mortality in 2 years). In addition, alloSCT itself entails serious discomforts and hazards for the patient since pre-transplant conditioning regimen and alloreactive T cells can predispose the subjects to suffer from various adverse events (GVHD, infections, and organ toxicity) any time after alloSCT irrespective to the study intervention. The investigational component of this transplant protocol ultimately aims to improve graft versus leukemia effect and overall survival; however, IFN- $\gamma$  may theoretically induce GVHD after alloSCT especially when concurrently used with donor lymphocyte infusions. Clinically, this approach is ethically acceptable because we will target a patient group with hematologic malignancies for which no therapy offers a greater than 10% chance of long-term survival. Subjects will make an informed decision to opt for a procedure which they understand has not been studied before, but which has a strong preclinical rationale. Risks of potential toxicity from IFN- $\gamma$  will be fully explained in the consent. Implicit in this decision is the opportunity to weigh all treatment options after full information has been given to them by the research team and the referring physician. Therefore, for the adult subjects on this protocol, the research involves greater than minimal risk to subjects with the prospect of direct benefit (45 CFR 46.102).

The IRB will be notified of any change in risk/benefit ratio affecting decisions about study continuation. If any literature becomes available, which suggests that conducting this trial is no longer ethical, the study will be terminated, and the IRB will be notified of the new findings.

Minimal risks and greater than minimal risks related to this protocol are listed in sections 11.1–11.5.

### **11.1 Risks Related to Interferon-gamma (greater than minimal risk)**

Anticipated risks from interferon-gamma are summarized in section 9.2.2. Additional risk in this protocol includes the potential for de novo or exacerbation of acute or chronic GVHD, flu-like symptoms, auto (allo-) immune disease, and organ toxicity.

### **11.2 Risks Related to Saliva Collection (negligible risk)**

No major or minor risks are involved with saliva collection.

### **11.3 Risks Related to Phlebotomy or Bone Marrow Examination (minimal risk)**

No major risks are involved with blood removal by intravenous puncture or bone marrow aspiration. Minor complications include bleeding, pain, itchiness, hematoma formation at the phlebotomy or bone marrow aspiration site, light-headedness, fainting, and nausea due to vasovagal reactions, and local infection.

### **11.4 Risks Related to Nucleotide Sequencing (minimal risk)**

Genetic information can have implications regarding health, identity, paternity, employability, or insurability for the research participant as well as family members. No such relationship will be known to exist for any of the genes we are testing or will test. The nature of the genetic testing detailed in the protocol will not put participants at any further risk. Nucleotide sequence variations to be determined in this study are not known to be associated with any known diseases. Genetic information revealed to the investigators cannot be meaningfully interpreted outside the narrow focus of the research and will not be provided to the healthy volunteers or their physicians.

